### Safety evaluation

2.12

Since TN and PT are both non-invasive external treatments, the side effects are minor, but in the course of operation, if the technique is misused, there may be accidents such as muscle, bone, or joint damage of the spine or other parts of the body. Therefore, the response to an adverse event should strictly follow the standard operating requirements to prevent accidents.

Pre- and post-treatment of each treatment session, the researchers will review the patient's symptoms according to the following safety classification:

Level 1: Safe, without any adverse reactions and treatment can continue.Level 2: Relatively safe, with minor adverse reactions, treatment can be continued without any additional remedial treatment for the injury.Level 3: There are safety problems, moderate adverse reactions, and treatment can continue after treatment of the injury.Level 4: Suspension of participation in research due to adverse reactions.Adverse events such as changes in pain, syncope, vertigo, and lumbar function degradation, will be carefully recorded in the case report form.

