### Follow-up

2.13

To evaluate the interventions’ short-term efficacy and safety, we will follow up with participants for 3 months after the trial. In the 20th week, the outcome assessor will telephone participants to investigate their low back pain recurrence. Patients can also inform the assessors of their clinical symptoms and AEs face to face or by email, text message, or WeChat.

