### Statistical analyses

2.16

The analysis set will consist of a full analysis set (FAS), a per-protocol set, and a safety set. The safety set will include randomly assigned participants and receive at least one intervention treatment. The FAS will consist of data indicating that the treatment was as close to the intention to treat as possible. In addition to meeting the safety set criteria, the participants must have been evaluated for the primary outcome at least once at the baseline. The FAS will be used in the primary analysis. For missing data, we will analyze the underlying reason and use an imputation adjustment approach, and the last observation carried forward analysis will be used to handle the missing data. After the primary analysis, a sensitivity analysis will be performed by comparing the results from the per-protocol analysis and the intention to treat analysis to evaluate the impact of missing data on the trial results. Besides, subgroup analyses by the center will be done.

(1)Statistical analysis methodFor all of the analyses, SAS version 9.4 was used. The confidence interval will be established at 95%, and the significance level at 0.05.Continuous variables were analyzed with an ANOVA test if normally distributed (results are presented as means ± SD) or Kruskal-Wallis H test if not normally distributed (presented as median with interquartile range). Multiple comparisons were addressed using the Tukey post hoc test (for ANOVA), and Bonferroni correction (for Kruskal–Wallis). The classification count data is checked by the chi-square test. This study used a one-sided test. When *P* < .05, the difference was considered statistically significant.(2)Statistical analysis contenta.Baseline evaluation: Social demographic characteristics, baseline severity analysis.b.Efficacy evaluation: We use the low back pain VAS score sheet, spinal ROM sheet, ODI scale, SF-36 scale, and the number of treatment sessions.c.Safety evaluation: Evaluation was made by the incidence of adverse events or recurrence of pain, or further injury from accidents during the follow-up period, and the level of safety.d.Compliance evaluation: Evaluation was carried out using the compliance rate.

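### Recurrence of pain is counted in the safety incidence, which mixes loss of benefit with harm and tends to count against the arm with more responders

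*Protocol article*

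**What the plan says.** All references are to the protocol article.

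- **Statistical analyses (2.16), item (2)c, safety:** "Evaluation was made by the incidence of adverse events or recurrence of pain, or further injury from accidents during the follow-up period", together with the level of safety.
- **Same section, item (2)b, efficacy:** "We use the low back pain VAS score sheet, spinal ROM sheet, ODI scale, SF-36 scale, and the number of treatment sessions". Recurrence is not in this list.
- **Same section, analysis set and test:** "The safety set will include randomly assigned participants and receive at least one intervention treatment", and, for categorical data in general, "The classification count data is checked by the chi-square test".
- **Follow-up (2.13):** "In the 20th week, the outcome assessor will telephone participants to investigate their low back pain recurrence". The section gives the purpose of follow-up as both short-term efficacy and safety. It does not say what counts as a recurrence.
- **Safety evaluation (2.12):** "Adverse events such as changes in pain" are recorded, along with syncope, vertigo and loss of lumbar function. This section describes a symptom review before and after each treatment session.

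**The concern.** Every participant enters with back pain of more than 12 weeks' duration (Inclusion criteria, 2.4). A patient whose pain never eased has persistent pain, not recurrent pain. If recurrence carries its ordinary meaning and the denominator is all treated patients, that patient is free of a recurrence event. A patient who improved and then relapsed is counted as having one. The better a treatment works, the more of its patients can have the event.

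The safety incidence would then contain two different things: harm from manual treatment, and fading of benefit after treatment stops. A difference between arms could not be assigned to either. The Introduction states the trial's purpose as evaluating both effectiveness and safety, so a misleading safety comparison bears on one of its two stated aims.

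**Working it through.** **The plan's own figures.** The article gives no recurrence or adverse event rate, so there is no stated figure on this point to reproduce. The group sizes come from Sample size calculation (2.7). A one-way ANOVA with means 1.4, 1.9 and 1.65, common SD 0.85 and alpha 0.05 needs 57 per group (power 0.802). Then 57/(1 − 0.15) rounds up to 68. Over three centres this is 204 per arm randomised and 3 × 57 = 171 per arm evaluable.

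**Formula.** With all treated patients in the denominator,

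incidence of recurrence = P(improved) × P(recurrence given improved).

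**Illustration 1: assumed response rates.** 60% against 40% improve, and 30% of improvers relapse in both arms.

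- Incidence: 0.60 × 0.30 = 0.18 and 0.40 × 0.30 = 0.12.
- Two-sided 5% two-proportion test, 204 per arm. The pooled proportion is 0.15. The standard error under no difference is √(2 × 0.15 × 0.85/204) = 0.0354. Under the alternative it is √((0.18 × 0.82 + 0.12 × 0.88)/204) = 0.0352.
- Probability of a significant result: Φ((0.06 − 1.96 × 0.0354)/0.0352) = Φ(−0.26), about 0.40.

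Varying the assumptions:

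| Improved | Relapse among improvers | n per arm | Flagged |
|---|---|---|---|
| 60% v 40% | 20% | 204 | 27% |
| 60% v 40% | 30% | 204 | 40% |
| 60% v 40% | 40% | 204 | 52% |
| 60% v 40% | 30% | 171 | about 35% |
| 60% v 40% | 30% | 57 (one centre) | about 15% |
| 60% v 50% | 20% to 40% | 204 | 10% to 16% |

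**Illustration 2: response rates from the plan's own VAS changes.** Take the changes as normal with the means and SDs of section 2.7: TN 1.4 (0.8), PT 1.65 (0.85), T&P 1.9 (0.9). Assume that improvement means at least 1.5 points on that scale, and that 30% of improvers relapse in every arm.

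| | TN | PT | T&P |
|---|---|---|---|
| Improved | 45.0% | 57.0% | 67.2% |
| Recurrence over all treated | 13.5% | 17.1% | 20.1% |
| Recurrence among improvers | 30% | 30% | 30% |
| Not improved, or relapsed, over all | 68.5% | 60.1% | 53.0% |

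The arm assumed to do best ranks worst on recurrence over all treated, and best on the last row. At 204 per arm, T&P against TN is flagged in 43% of trials, PT against TN in about 17%, and T&P against PT in about 12%. For T&P against TN, cut-offs of 1.0 to 2.0 and relapse rates of 20% to 50% give 13% to 87%.

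**When the ordering changes.** The two incidences are equal when the relapse rate among T&P improvers, divided by that among TN improvers, equals P(TN improved)/P(T&P improved). At the 1.5-point cut-off this is 0.450/0.672 = 0.67, or about 20% against 30%. It is 0.82 at a 1.0-point cut-off and 0.50 at 2.0. Below these ratios the better arm shows the lower incidence.

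**If any pain at the week-20 call counts.** Assume that non-improvers still have pain. In illustration 1 the incidence becomes 1 − 0.60 × 0.70 = 58% against 1 − 0.40 × 0.70 = 72%. The bias reverses, and the item is simply an efficacy result reported as safety.

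**The case against.** **The rule is partly inferred.** The article does not state a denominator for recurrence, does not define it, and names no specific between-arm test of it. The list joined by or could be tabulated item by item, and a full protocol or analysis plan may define the term. This stands as a limit on the size of the problem. It does not remove the problem: the article itself assigns recurrence to safety, leaves it out of efficacy, and makes the safety set everyone treated. Tabulating it separately under safety would still present loss of benefit as harm.

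**Stronger readings a reader might infer.** Three are not supported.

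- *The more effective arm will look less safe.* This needs the ordinary meaning of recurrence and similar relapse rates among improvers. The article gives neither, and the break-even ratios above show that the ordering can reverse.
- *The telephone question is the only week-20 measure, so durability cannot be assessed.* Data collecting and monitoring (2.14) and the Figure 1 caption both name a 3-month post-intervention assessment. Outcome measurements (2.11) refers to Figure 2 for the time points, and its caption lists VAS, ODI, ROM and SF-36. The figure is not available here, so pain at 3 months cannot be called missing.
- *Pain changes should leave the safety evaluation too, because pain enters safety twice.* Section 2.12 records them in the context of the per-session symptom review. Worsening after manual treatment is a plausible direct harm, distinct from relapse months later, and dropping it would lose a real signal.

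**The size is illustrative.** The 40% uses 204 per arm without loss, and is lower with the planned dropout, within one centre or with closer response rates. This is correct.

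**Conclusion.** The point holds in a limited form. As written, the safety incidence includes an event that, on its ordinary meaning, only responders can have. It therefore mixes loss of benefit with harm and tends to count against the arm with more responders. The 18% against 12% example, flagged in about 40% of trials at 204 per arm, rests on assumed response and relapse rates and on all treated patients being the denominator. Other plausible settings give anything from about 10% to 87%, and the direction can reverse. Under either meaning of recurrence, the item measures durability of effect and does not belong in a safety incidence. The consequence is confined to the safety summary. The primary VAS analysis does not depend on it, so the change is advisable but does not put the trial's main result in question.

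**What to change.** - In Statistical analyses (2.16), item (2)c, remove recurrence of pain from the safety incidence. Keep adverse events (including pain worsening recorded with the treatment sessions), injuries and the safety level.
- Add durability to item (2)b as an efficacy outcome in the full analysis set. Use either the 3-month pain score, or the proportion improved at week 8 and still improved at week 20 with all patients in the denominator. State the improvement threshold.
- Define recurrence by an improvement threshold and a return threshold. Report it among improved patients descriptively only, because that group is selected by a post-randomisation result.

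The cost is a few lines of analysis wording. If the schedule in Figure 2 already includes VAS at 3 months, no new data item is needed. If it does not, one verbal pain score can be added to the call already planned.

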## Discussion

3

CNLBP is a significant health issue worldwide. Given its prevalence, the need to assess practical approaches for low back disorders is of prime importance. TN is one of the essential parts of TCM and has contributed to people's health in China for thousands of years. A considerable body of scientific evidence supports such therapies for CNLBP treatment, but their efficacy has not been established.^[35]^ Therefore, it is essential to provide robust evidence about the effectiveness of TN for CNLBP.

The present trial is a comparative effectiveness study of TN (intervention) and PT (control) for pain relief and functional recovery in patients with CNLBP. We evaluated 3 aspects of CNLBP: pain, physical function, and quality of life. The VAS will be used as the primary outcome. The secondary outcomes are the ODI, which measures dysfunction and includes 10 questions on daily activities; the ROM, which evaluates functional limitations in everyday life; and the SF-36, which measures changes in health-related quality of life.

According to the theory of TCM,^[35]^ good physical health depends on qi and blood circulation. The common causes of pain are stagnation of qi and stasis of blood. Moreover, other pathogenic factors such as phlegm and dampness can be identified as causative factors in a blockage. TN can relieve pain by promoting qi and blood's local and systemic circulation by removing pathogenic factors. Studies have shown that TN may alleviate CNLBP by reducing inflammation and repairing damaged mitochondria in the skeletal muscle.^[36]^

The results of this RCT will contribute to the clinical practice of TN for CNLBP. And the results will be presented in an open-access peer-reviewed journal and an academic conference.
